###### Qualitative Analysis of Semistructured Interviews

Patient interviews will be transcribed and analyzed using qualitative content analysis. Specifically, interviews will be coded and categorized into 2 groups representing functioning and nonfunctioning NETs patient responses. Similar codes across the 2 categories for functioning and nonfunctioning NETs patients will then be explored as global themes informed by ground theory [54,55]. Coding labels will be created by 2 independent experienced qualitative researchers, who will examine and discuss each other’s coding and thematic analysis to promote rigor and interrater reliability [56].

#### Phase 2: Development of the Nurse-Led Phone-Based Intervention

In collaboration with the Unicorn Foundation, this study will develop and pilot test an intervention to augment this service.

##### Unicorn Foundation

The Unicorn Foundation is an Australian not-for-profit medical foundation that aims to educate and support people who have a NET, as well as their families, by promoting better awareness and knowledge of the disease. The Unicorn Foundation advocates research in the area and has worked with clinical researchers to raise money and fund pilot testing of NET clinical trials. In addition, the foundation independently funds the employment of a registered nurse, offering the support of a NET Nurse hotline.

Current utilization of the NET Nurse hotline has been estimated by the Unicorn Foundations data monitoring at approximately 350 incoming calls over a 6-month period, with callers originating across all Australian states and territories. In addition, the location of callers is estimated at 59% from metropolitan areas and 41% of callers from rural areas, where access to NET-specialized physicians is likely to be limited. In addition, the Unicorn Foundation website offers a range of online resources such as updates on current NET research, access to support groups, and information on NETs.

The accessibility to this service nationally makes it an optimal avenue for disseminating and implementing evidenced-based approaches to provide better quality of care for those accessing information. This study will expand upon this service and provide a more structured response for patients with information that is tailored to meet the needs of NET patients based on their clinical characteristics and from information that has been derived from both clinical and patient-reported outcome data collection.

##### Development Framework

In line with the Schofield and Chambers framework, the design and development of the intervention will be guided by the 7 key features required to achieve effective translation into usual care and practice [40]:

Targeting cancer type and stage: To gain an understanding of the problem, patients recruited to the study are classified as either functioning or nonfunctioning by their treating oncologist based on their clinical presentation of distinctive hormonal syndromes and symptoms associated with functioning NETs [9,11,19-21] versus the asymptomatic profile of nonfunctioning NETs [23]. Intervention content will be developed based on quantitative and qualitative data on patient experiences and care preferences. The intervention will target the 2 subgroups and provide tailored supportive care around aspects of information on their disease, symptom burden, and self-care management.Tailoring to individual’s unique needs: The delivery of the intervention will be tailored to suit individual needs. NET patients utilizing the Unicorn Foundation website will have access to online information and tools to access support. Users will be triaged online via the website based on symptom severity and distress. Relevant information will be delivered online as part of the intervention content will be tailored in depth based on the first phase of triaging. If the patients’ needs or concerns are not resolved, the intervention approach will be progressively stepped up to the top tier, which will be a phone-based nurse follow-up. In adopting this approach, the nurse will be able to prioritize the most vulnerable patients, increasing efficacy of the service and making patient encounters more meaningful and useful.Promoting self-management: Promoting self-management of disease by providing patients with the resources and skills to address issues around symptom assessment, problem solving, and goal setting may reduce distress and ultimately health care use by enhancing the uptake of health behaviors [50,51]. The intervention will provide users with online information and resources to help facilitate self-assessment and symptom management. Nurse-led phone-based follow-up will also use motivational interviewing techniques to enhance self-management behavior change by adopting a client-centered method thought to encourage self-motivation [52].Efficient intervention delivery: The delivery method of this intervention utilizes existing resources and infrastructure via the Unicorn Foundations website and Nurse Hotline service. Using this method of delivery adopts a low-intensity approach, improving efficiency by being a tool that can be easily integrated as an ongoing clinical service.Ensuring evidence-based and theoretical grounding: The content of the intervention will be based on theory and available evidence. Content development will be based on analysis of both quantitative and qualitative data collected in the prospective cohort study that will describe the psychosocial, QoL, and clinical characteristics of patients with functioning and nonfunctioning NETs. Patient experiences and care preferences reported during semistructured interviews will also form part of the deliverable content of the intervention. The delivery mode is likely to incorporate media visual, textual, and diagrammatic resources and one-to-one telephone support. For example, the intervention may include patient experience videos, flowchart diagrams of treatment pathways, and fact sheets.Specifying protocol training and adherence: A standardized manual for the one-to-one nurse-led telephone consultations will be developed, specifying the (1) content of the intervention consisting of, but not limited to, a description of NETs and their subgroups, method of triaging patients, symptom burden, patient care preferences, assessment of needs, and coaching in relevant self-care strategies and (2) training and supervision procedures. The development of a protocol of standardized content and training will ensure a comprehensive knowledge base and consistent reproducible delivery of the intervention content.Confirming stakeholder acceptability: Stakeholder acceptability will be optimized throughout the design process by involving consumers, consumer advocacy group, allied health professionals, medical oncologists, and clinical NET nurses in the development of the phone-based nurse-led intervention [53,57]. All members of the stakeholder committee will also review iterative revisions of the intervention and resource manuals.

#### Phase 3: Pilot/Feasibility Study

##### Study Setting

The study will be conducted via the Unicorn Foundation website.

##### Pilot Testing of Intervention

###### Pretesting the Intervention

Online triaging will be tested by the research team to ensure functionality. A nurse with experience managing NET patients will be trained in intervention delivery, including confirming eligibility of callers, assessing the online triage, and delivery of intervention material. The nurse will also be trained on eliciting and responding to emotional and informational cues, goal setting, and motivational interviewing and will receive feedback on practice sessions. All intervention content will be recorded for quality assurance.

Over a 12-week period, 20 callers will be recruited via the Unicorn Foundation Nurse Hotline and invited to participate in a small-scale pilot study. Callers will be screened to determine their eligibility to participate. Eligibility criteria will be the same as used in phase 1, with the addition of the participant being able to speak as well as understand English to ensure comprehension and effective communication via the Nurse Hotline. Once eligibility is confirmed, callers will be given access to the online triage tool, which will determine the intervention content that will be delivered. Participants will also have the option to receive a nurse-led phone-based follow-up to address any ongoing concerns.

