###### Assessment of Successful Implementation

The success of the implementation of the intervention will be assessed based on the taxonomy of 8 conceptually distinct implementation outcomes. These consist of, acceptability, adoption, appropriateness, feasibility, fidelity, implementation cost, penetration, and sustainability [58,59]. Of these outcomes, 3 will be assessed to determine the successful implementation of the intervention. These consist of (1) acceptability and satisfaction with various aspects of the intervention; (2) appropriateness, relevance, and suitability of the intervention; and (3) feasibility, practicability, and suitability for everyday use of the intervention [58,59].

Measurement of the acceptability appropriateness and feasibility domains will consist of a semistructured interview. Both the participants and the provider will be questioned on their level of satisfaction with the content and its delivery as well as the usefulness and practicability of the material. The number of people invited to participate in the pilot study and the percentage who consent to participate will be recorded as a measure of feasibility and indication for suitability of everyday use.

Interviews will be transcribed, coded, and categorized into 2 groups representing functioning and nonfunctioning NETs patient categories. Similar codes across the 2 categories for functioning and nonfunctioning NETs patients will then be explored as global themes informed by ground theory [54,55]. Coding labels will be created by 2 independent experienced qualitative researchers, who will examine and discuss each other’s coding and thematic analysis to promote rigor and interrater reliability [56]. These analyses will be used to iteratively refine the intervention.

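### The pilot enrols only hotline callers and reads their consent as a sign of everyday suitability; it cannot observe website entry and names no measure of online resolution or step-up to the nurse

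*Protocol article*

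**What the plan says.** **Intended service.** Under Phase 2, Development Framework, the service begins online: "Users will be triaged online via the website based on symptom severity and distress". Information matched to the triage result follows. If concerns remain, "the intervention approach will be progressively stepped up to the top tier, which will be a phone-based nurse follow-up". The stated gain is that "the nurse will be able to prioritize the most vulnerable patients, increasing efficacy of the service".

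**Pilot.** The Phase 3 Study Setting is one sentence: "The study will be conducted via the Unicorn Foundation website". Under Pretesting the Intervention, recruitment is by telephone: "Over a 12-week period, 20 callers will be recruited via the Unicorn Foundation Nurse Hotline and invited to participate in a small-scale pilot study". The nurse is "trained in intervention delivery, including confirming eligibility of callers, assessing the online triage, and delivery of intervention material". The order of contact is then given: "Once eligibility is confirmed, callers will be given access to the online triage tool, which will determine the intervention content that will be delivered". Nurse follow-up by phone is afterwards offered to participants as an option for any concerns that persist.

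**Measures.** Assessment of Successful Implementation lists eight implementation outcomes and selects three: acceptability, appropriateness and feasibility. All three are assessed by semistructured interview with the participants and the provider. One quantitative element is added: the number invited is recorded, and "the percentage who consent to participate will be recorded as a measure of feasibility and indication for suitability of everyday use".

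**The concern.** Two things do not fit together.

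First, the intended population enters at the website and the pilot population enters by phone. Someone who has already called may differ from a website visitor in how willing they are to work through an online tool and in how likely they are to want the nurse afterwards. The article gives no data on the size or direction of any such difference, and a pilot with one entry route cannot show it.

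Second, the consent percentage is given a meaning that it cannot carry. It is the share of invited callers who agree to join a study. A routine user of the service gives no research consent. A caller may decline the study and still use the tool, or consent and then abandon it.

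At stake is the conclusion on feasibility. The Discussion says that the work will lead to a large randomised trial. If the pilot is reported as showing that the stepped service suits everyday use, that statement would rest on a consent rate among callers and on interviews with people who all arrived by phone.

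**Working it through.** The pilot size of 20 comes with no derivation, precision target or success threshold, so there is no figure of the plan's own to reproduce. The check is a comparison of the stated sequences, followed by arithmetic on what the measures could yield.

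**1. Sequence as intended and as piloted**

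| Step | Intended service (Development Framework) | Pilot (Pretesting the Intervention) |
|---|---|---|
| Entry | Website | Call to the hotline, eligibility screening |
| Next | Online triage | Online triage |
| Next | Tailored online content | Content determined by triage |
| Last | Nurse by phone if needs are unresolved | Nurse by phone as an option |

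The middle rows agree. The entry row differs. The last row differs in wording: a step conditional on unresolved need against an option open to participants. The two descriptions should be reconciled.

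**2. What each measure can observe**

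- Interviews: satisfaction with content and delivery, usefulness and practicability, among callers and the provider.
- Consent percentage: willingness of callers to join the study.
- Whether website visitors start triage: not observable, because recruitment is not at the website.
- Whether triage is completed, content is opened, needs are met online, or the nurse is then used: observable among the 20, but not named as measures.

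**3. Recruitment context**

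Input: about 350 incoming calls in 6 months (Unicorn Foundation section). Pro rata for 12 weeks: 350 × 12/26 = 161.5 calls. Twenty participants equal 20/161.5 = 12.4% of that volume. These are calls, not distinct or eligible callers, so 12.4% only shows scale.

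**4. What the consent percentage would look like**

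No consent rate is given for the pilot. Assume 30%, 50% or 80%, and take the 20 as the number enrolled. Number invited = 20 / rate, rounded. The exact (Clopper-Pearson) 95% interval for k of n runs from the 2.5% quantile of Beta(k, n − k + 1) to the 97.5% quantile of Beta(k + 1, n − k).

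| Assumed consent | Invited | 95% interval |
|---|---|---|
| 30% | 67 | 19% to 42% |
| 50% | 40 | 34% to 66% |
| 80% | 25 | 59% to 93% |

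None of these values says anything about use of the tool. The limitation is what is measured, not only its precision.

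**5. What added counts would look like**

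Same formula, n = 20:

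- 10 of 20 (50%): 27% to 73%
- 16 of 20 (80%): 56% to 94%
- 18 of 20 (90%): 68% to 99%

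If the 20 were divided evenly by entry route, 5 of 10 would give 19% to 81%. Such counts can expose a gross failure, such as most people not finishing triage, but cannot fix a rate closely.

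**The case against.** Five points can be made for the plan.

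- **Feasibility does not rest on consent alone.** Interviews with participants and the provider are the main instrument, and consent is an addition. This stands, and the point is confined to the quantitative measure.
- **Callers do go through the online tier.** After screening they meet triage, then content, then the nurse if they wish. This stands. A reader might infer that the pilot can say nothing about whether the pathway works; the article does not support that, because the tool and content are used and discussed by real callers.
- **Uptake is openly out of scope.** Adoption and penetration are listed among the eight outcomes and not selected. This stands as a reason not to demand uptake estimates. It does not justify describing a consent rate as evidence of everyday suitability.
- **Callers belong to the target population.** The project is meant to extend an existing hotline, and delivery uses both website and phone. This also stands. The article does not say whether callers visited the website first, so it cannot be asserted that callers prefer the phone or that none has used the site. What is stated is only that recruitment is through the hotline.
- **An article condenses.** Usage logging for a tool not yet built may be set out in the full protocol. That is fair for the detail of logging. The recruitment route and the interpretation placed on consent are, however, stated outright.

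**Conclusion.** The point holds in a limited form. Recruitment is from hotline callers only (20 of 20), while the stated setting is the website and the service is designed to begin there. The pilot can inform acceptability and practicability of the triage tool and content among callers. It cannot observe website entry, and it names no measure of online resolution or step-up. The single quantitative feasibility measure reflects research consent among callers and does not indicate suitability for everyday use.

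This rests on the article's description being complete as to recruitment route and named measures. The consent rates in the working are assumed.

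Two stronger readings are not supported. A reader might infer that better measures would let this pilot supply planning figures for the randomised trial; with 20 people the intervals are too wide. A reader might also infer that the 20 places need a quota for functioning and nonfunctioning tumours. The only split stated is about half and half, expected for the Phase 1 clinics, and Phase 3 plans no quantitative comparison of the subgroups.

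**What to change.** **Assessment of Successful Implementation.** Report the number invited and the consent percentage as recruitment statistics only. Add as descriptive feasibility measures, each with an exact 95% confidence interval, the proportions of participants who:

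- complete online triage;
- open the tailored content;
- report their needs resolved online;
- go on to nurse follow-up.

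Keep the interviews as planned.

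**Pretesting the Intervention.** Either invite some of the 20 from the website triage page and describe results by entry route, or keep hotline recruitment and limit the feasibility conclusion to hotline callers.

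**Cost.** Minor logging from the tool and call records, plus a website invitation if that option is taken. The sample size need not change. The estimates will be imprecise, more so when divided by entry route, and should be presented as descriptive. Phases 2 and 3 were not yet completed when the article was written, so on that timing the change could be made before the pilot data are in.

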###### Assessment of Successful Implementation

The success of the implementation of the intervention will be assessed based on the taxonomy of 8 conceptually distinct implementation outcomes. These consist of, acceptability, adoption, appropriateness, feasibility, fidelity, implementation cost, penetration, and sustainability [58,59]. Of these outcomes, 3 will be assessed to determine the successful implementation of the intervention. These consist of (1) acceptability and satisfaction with various aspects of the intervention; (2) appropriateness, relevance, and suitability of the intervention; and (3) feasibility, practicability, and suitability for everyday use of the intervention [58,59].

Measurement of the acceptability appropriateness and feasibility domains will consist of a semistructured interview. Both the participants and the provider will be questioned on their level of satisfaction with the content and its delivery as well as the usefulness and practicability of the material. The number of people invited to participate in the pilot study and the percentage who consent to participate will be recorded as a measure of feasibility and indication for suitability of everyday use.

Interviews will be transcribed, coded, and categorized into 2 groups representing functioning and nonfunctioning NETs patient categories. Similar codes across the 2 categories for functioning and nonfunctioning NETs patients will then be explored as global themes informed by ground theory [54,55]. Coding labels will be created by 2 independent experienced qualitative researchers, who will examine and discuss each other’s coding and thematic analysis to promote rigor and interrater reliability [56]. These analyses will be used to iteratively refine the intervention.

##### Data Management

###### Data Monitoring

The study has received ethics approval from the Human Research Ethics Committee of Peter MacCallum Cancer Centre. No significant risks to participants are anticipated. Questionnaire responses will be scored within 3 working days of being received, so as to ensure that any high distress scores reported in questionnaires will be reported to the treating clinician and/or nurse coordinator in a timely manner. Participants may then be referred to receive treatment from a qualified psychologist; however, this procedure will be determined by, and is dependent upon, each site’s standard of care with respect to referral procedures.

### Safety

Any adverse or unexpected outcomes that occur as a result of the study will be documented, and copies will be provided to site investigators and the principal investigator within 24 hours. The principal investigator will proceed to report any such adverse event to the Human Research Ethics Committee.

### Ethics and Dissemination

Ethics approval was obtained from the Human Research Ethics Committee of Peter MacCallum Cancer Centre (project number 16/08L), Human Research Ethics Committee of the Northern Sydney Local Health District in New South Wales (project number RESP/16/73), Human Research Ethics Committee of the Central Adelaide Local Health Network in South Australia (project number Q20160901), Human Research Ethics Committee of Royal Perth Hospital (project number RGS0000000632), and Human Research Ethics Committee of the Royal Brisbane and Women’s Hospital (project number 17/QRBW/400). Results will be widely disseminated to the funding body and oncology conferences and meetings and through peer-reviewed publications.

## Results

Currently, the project is progressing through phase 1 and has completed recruitment. A total of 138 participants have been recruited to the study. To date, we have patient-reported outcome data from 122 participants at baseline and 87 participants at 6-month follow-up. Of these, qualitative data have been collected from 35 participants who consented to a semistructured interview. Phase 2 and phase 3 of the project are yet to be completed.

## Discussion

Limited research suggests that patients with NETs have significantly impaired QoL compared with the general population [30,60]. However, given the heterogeneity of this diagnosis and the broad spectrum of symptom severity patients may experience [11,21], current research also fails to delineate how this clinical variability impacts patient supportive care needs. This study will address and improve on the availability of disease-specific information as well as informing the design of supportive care tailored for the unique needs of the NET patient population. Using the Schofield and Chambers framework [40], a tailored intervention will be developed that will provide targeted supportive care for patients with NETs according to the clinical characteristics and psychosocial profile of patients with functioning and nonfunctioning NETs.

This research initiative will be the first concerted effort to differentiate the priorities and needs of patients with functioning and nonfunctioning NETs comparing the QoL, psychological morbidity, health care system experiences, and clinical profile of these 2 distinct NET patient subgroups. This project is innovative, and to our knowledge, this study is a world-first initiative that will collaborate with the NET national advocacy group, consumers, behavioral scientists, medical oncologists, and specialist NET nurses to iteratively design and pilot test a phone-based nurse-led intervention. The expected benefits of this study are that in combining the expertise across disciplines to form collaboration between medical oncologists, professional nurses, behavioral scientists, consumers, and consumer advocacy groups, this initiative capitalizes on multidisciplinary perspectives to develop a model that will improve the supportive care of patients with NETs.

To date, no research has delineated the differences between patients with functioning and nonfunctioning NETs in terms of their experiences, QoL, psychosocial, and daily functioning needs. Therefore, the development of an intervention that targets these differences and can provide tailored supportive care that is accessible to all patients across metropolitan and rural areas has the propensity to optimize current care.

The intervention will build on the existing Unicorn Foundation online platform and phone counseling to improve the current care of patients with NETs by providing targeted tailored support via the Unicorn Foundation website and nurse-led phone-based support hotline. This intervention also has the potential to be accessible to all patients irrespective of their demographical location. This initiative offers a novel, patient-centered approach to the supportive care of patients diagnosed with NETs that will lead the way nationally and internationally. This work will lead to a large-scale randomized controlled trial to evaluate the impact of this novel intervention on patient health outcomes.

